### Statistic analysis

SPSS and Excel will be used to perform the statistical analysis. A probability less than 0.05 will be considered to be significant. Data will be presented for the two arms of the study group. Data will be expressed as means +/− standard deviation and proportions or rates. The analysis will be by intention to treat.

Descriptive analysis will be used to assess the prevalence of predefined minor intrauterine abnormalities at SIS and office hysteroscopy. Comparisons between the two arms of the randomised group will be done by applying Chi-square testing to crude rates of cumulative implantation and ongoing pregnancy and by using life table analysis to account for the factor of time to implantation or pregnancy. The difference in tolerability of SIS will be compared to the tolerability of diagnostic and therapeutic hysteroscopy making use of the Student’ *t*-test analysis of the VAS score.

The relative contribution of predefined cavitary abnormalities versus other predictive factors like female age and duration of infertility will be assessed by univariate and multivariate logistic regression and Cox regression.

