**Methods/design:**

Multicenter randomised controlled trial in asymptomatic subfertile women, indicated for a first IVF/ICSI treatment cycle, with normal findings at transvaginal sonography. Women with recurrent miscarriages, prior hysteroscopy treatment and intermenstrual blood loss will not be included. Participants will be randomised for a routine fertility work-up with additional (SIS and) hysteroscopy with on-the-spot-treatment of predefined intrauterine abnormalities versus the regular fertility work-up without additional diagnostic tests. The primary study outcome is the cumulative ongoing pregnancy rate resulting in live birth achieved within 18 months of IVF/ICSI treatment after randomisation. Secondary study outcome parameters are the cumulative implantation rate; cumulative miscarriage rate; patient preference and patient tolerance of a SIS and hysteroscopy procedure. All data will be analysed according to the intention-to-treat principle, using univariate and multivariate logistic regression and cox regression. Cost-effectiveness analysis will be performed to evaluate the costs of the additional tests as routine procedure. In total 700 patients will be included in this study.

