## Methods

### Study design

The inSIGHT trial is a multicenter randomised controlled trail (RCT). A total of twenty-five academic and non-academic centers in the Netherlands will participate. An economic analysis is incorporated to assess the cost-effectiveness of the investigated tests as routine procedures prior to IVF. Inclusion was started in May 2011.

This study will be conducted according to the principles of the Declaration of Helsinki and in accordance with the Medical Research Involving Human Subjects Act (WMO). The study protocol has been approved by the medical ethical review committee of the University Medical Center Utrecht (MEC 10–272) and by the board of directors of all participating centers. The protocol is registered at clinicaltrial.gov NCT01242852.

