### Recruitment, consent and randomisation

Women with an indication for a first IVF/ICSI treatment cycle will be informed about this trial by their attending physician. They will also receive written patient information. One to two weeks after the first visit, the coordinating investigator will counsel the woman. If a woman agrees to participate in the study, informed consent will be obtained and randomisation will be performed for one of two strategies: routine infertility work-up followed by immediate IVF (control arm) or the routine work-up with additional diagnostic tests ((SIS and) hysteroscopy) with on-the-spot treatment of intrauterine pathology followed by IVF (intervention arm) (Figure 1). Randomisation will be performed centrally by a web-based randomisation program and will be stratified according to recruiting center.

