## Statistical analysis

### Sample size calculation

Based on the literature, the increase in ongoing pregnancy in women with recurrent IVF failure after treatment of predefined abnormalities of the uterine cavity is found to be 9–32% in the subsequent IVF/ICSI cycles [5,7,9].

In a group of women indicated for a first IVF/ICSI treatment cycle, the difference in cumulative live birth rate after 18 months of IVF/ICSI treatment is estimated to be 10% between the patients with and without hysteroscopy (40% versus 30%). The number of patients needed to have 80% power (with alpha = 0.05) to detect such a difference is 350 per study arm.

To be able to answer the question on the benefit of using SIS as a pre-selection tool the following sample size calculation for patients needing to have both SIS and hysteroscopy was made. From previous literature, the prevalence of unsuspected intrauterine abnormalities is considered to be 12% and the sensitivity of SIS compared to hysteroscopy to be 95% [11]. SIS and hysteroscopy need to be performed in 160 women to achieve a 95% confidence interval of 10% (85–100%). This means that a total of 320 women need to be randomised in the five hospitals in this study that perform SIS.

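### The arms are compared by an unstratified chi-square although randomisation is stratified by centre and prognostic factors are named: the test is valid and adequately powered, but forgoes a few points of power that cost nothing to recover

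*Protocol article*

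**What the plan says.** Under Recruitment, consent and randomisation, allocation "will be stratified according to recruiting center"; no other stratification factor is given. Study design sets the number of strata: "A total of twenty-five academic and non-academic centers in the Netherlands will participate".

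The section Statistic analysis compares the arms in two ways. The first is a test of proportions: "applying Chi-square testing to crude rates of cumulative implantation and ongoing pregnancy". The second takes timing into account and is a life-table analysis. Neither is said to take account of centre or of any baseline factor. Regression appears in a separate paragraph with a different task, weighing cavitary abnormalities against "other predictive factors like female age and duration of infertility will be assessed by univariate and multivariate logistic regression and Cox regression".

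The abstract's Methods/design paragraph is broader: "All data will be analysed according to the intention-to-treat principle, using univariate and multivariate logistic regression and cox regression". It names no covariates and does not say whether an adjusted comparison of the arms is meant.

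The Sample size calculation rests on a difference "estimated to be 10% between the patients with and without hysteroscopy (40% versus 30"%), with 80% power, alpha 0.05 and 350 women per arm.

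**The concern.** Stratified randomisation balances the arms within each centre, so differences in success rate between centres largely drop out of the treatment difference. A crude chi-square still counts those differences as noise. Its standard error is then somewhat too large, and the test rejects slightly less often than 5% under the null.

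Age and duration of infertility are a separate matter. They are not stratification factors, so ignoring them leaves the level of the test alone but forgoes the precision that adjustment would bring.

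Two things are at stake: a few points of power that need no further recruitment, and clarity about which arm comparison is primary, since the abstract speaks of regression for all data while the body tests the arms by chi-square and life table.

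**Working it through.** **1. The plan's own figure.** With 40% and 30%, two-sided alpha 0.05 (sidedness is not stated, but two-sided reproduces the figure) and pooled variance under the null:

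n per arm = [1.960·√(2·0.35·0.65) + 0.842·√(0.40·0.60 + 0.30·0.70)]² / 0.10² = [1.322 + 0.565]² / 0.01 ≈ 356.

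At 350 per arm, the null SE is √(0.455/350) = 0.03606 and the alternative SE is √(0.45/350) = 0.03586. Power = Φ[(0.10 − 1.960·0.03606)/0.03586] = Φ(0.818) = 79.3%. The stated 350 is therefore the size for an unadjusted chi-square, to within rounding. Design and test match.

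**2. Level of the crude test.** Suppose centre explains a share R² of outcome variance and the arms are balanced within centre. The true variance of the difference is (1 − R²) times what the crude test assumes, so its level is 2·[1 − Φ(1.960/√(1 − R²))]:

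| R² (assumed) | Level of crude test |
|---|---|
| 1% | 0.049 |
| 2% | 0.048 |
| 5% | 0.044 |
| 10% | 0.039 |

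A between-centre log-odds SD s corresponds to first order to R² ≈ p(1 − p)·s². With p = 0.35 this is 0.2275·0.09 = 2.0% at s = 0.3 and 0.2275·0.25 = 5.7% at s = 0.5. Simulation with 20,000 runs gives a level of about 4.4% at SD 0.5, 3.8% at SD 0.7, and nominal at 0.3 or less.

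**3. Power, centre only.** Simulation used 25 centres of 28 women (700/25), exact 1:1 balance within centre, overall rates held at 30% and 40%, and 6,000 runs per setting:

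| Centre SD (log-odds, assumed) | Crude chi-square | Mantel-Haenszel by centre | Gain (points) |
|---|---|---|---|
| 0.2 | 78.9% | 79.1% | 0.2 |
| 0.3 | 80.1% | 80.6% | 0.5 |
| 0.5 | 79.6% | 81.0% | 1.4 |
| 0.8 | 81.3% | 84.3% | 3.0 |

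Uneven centres give the same pattern. These follow the saline infusion sonography target: five hospitals of 320/5 = 64 women and twenty of (700 − 320)/20 = 19. With those sizes, SD 0.7 gives 80.3% crude against 82.9% stratified, a gain of 2.6 points.

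**4. Power, centre and age.** The adjusted analysis is a linear model for the risk difference with centre effects, age and robust standard errors:

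| Centre SD | Age log-odds per SD | Crude | Adjusted |
|---|---|---|---|
| 0 | 0.5 | 80.0% | 82.0% |
| 0.3 | 0.3 | 79.3% | 80.9% |
| 0.3 | 0.5 | 79.5% | 81.9% |
| 0.5 | 0.5 | 79.6% | 83.5% |
| 0.8 | 0.5 | 80.6% | 85.0% |

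Age alone adds about 2 points at 0.5 per SD (first row). The total gain is 1.6 to 4.4 points over these settings.

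**5. In sample-size terms.** The need per arm is 356·(1 − R²). If all covariates together explain 2%, 5% or 10% of outcome variance, it falls to about 349, 339 or 321.

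**The case against.** The best defence is that a prespecified crude chi-square is simple, transparent and never exceeds its nominal level, and that the sample size was calculated for it. All of that stands. So does the point that every gain above rests on assumed heterogeneity and age effects.

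A reader might infer that power falls below the stated 80%. It does not: with overall rates held at 30% and 40%, crude power stays at about 79% to 81% in the settings above. A simulation can suggest otherwise if it fixes 30% and 40% in an average centre and then adds random centre effects. At SD 0.5 that gives overall rates of 30.96% and 40.54%, a difference of 9.58 points, so power drops because the effect was made smaller. Nor does the 79.3% at 350 per arm indict the test; it reflects rounding in the sample size.

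A reader might also infer that ignoring age makes the test conservative. Age is not a stratification factor, so only power is affected.

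It can be argued that the abstract already promises regression, or that the detail belongs in an analysis plan not shown. But the article states its test rather than leaving it open, and the body gives regression another task. The abstract's sentence does not describe an adjusted arm comparison. It does not flatly contradict the body either; the two leave the role of regression unclear.

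Small centres are a fair worry for a model with 25 centre terms, but Mantel-Haenszel handles them without pooling.

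**Conclusion.** The point holds as one of efficiency and prespecification, not validity. The stated comparison ignores the factor by which women are randomised and the prognostic factors that the plan itself names. It is conservative only through centre, and only if centres differ materially. The power forgone is measured against a stratified or adjusted analysis, not against the planned 80%: about 0 to 1.4 points from centre at SD up to 0.5, about 3 at SD 0.7 to 0.8, and about 2 more from age at a log-odds of 0.5 per SD.

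These sizes assume effective 1:1 balance within centre, overall rates of 30% and 40%, and the stated heterogeneity and age effects, none of which the documents supply. No effect of duration of infertility was simulated. At modest centre heterogeneity and a weak age effect the gain is close to nil, but the change has no material downside.

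**What to change.** - Name one primary arm comparison that follows the design. Either use a Cochran-Mantel-Haenszel test with a risk difference stratified by centre, or a logistic model with arm, centre (random intercept, or small centres pooled by a rule set in advance), female age and duration of infertility, reported as a marginal risk difference.
- Stratify the life-table or other time-to-event comparison by centre.
- Keep the crude chi-square as a supportive analysis.
- Reword the abstract's regression statement and the section Statistic analysis so that both say the same about the role of regression in comparing the arms.

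The cost is a few sentences, settled before outcome data are seen. Centre is known from randomisation, and age and duration of infertility are already needed for the planned regressions. The sample size need not change.

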## Discussion

Despite the great advances in the field of IVF/ICSI, implantation failure is still high. This not only causes considerable stress to the woman but is also associated with high costs of the fertility treatment. The uterine cavity is considered to play an important role in successful implantation. Even minor abnormalities, such as endometrial polyps, submucous myomas, adhesions or septa, are thought to impair the chance to conceive [2]. Studies have shown a high prevalence of unsuspected intrauterine abnormalities prior to IVF [3-12,23]. In addition, two RCTs reported improvement in pregnancy rates after hysteroscopy in the subsequent IVF cycle in patients with two previous failed IVF attempts. Currently, hysteroscopy is not recommended as routine investigation in the fertility work-up because of a lack of robust evidence. The present inSIGHT study is a large randomised controlled trial in which the effects on pregnancy rates and costs of SIS and hysteroscopy will be studied. The results of this study, which are expected in 2015, will help to clarify the significance of hysteroscopy prior to IVF/ICSI treatment.

## Abbreviations

IVF, In vitro fertilisation; ICSI, Intracytoplasmic sperm injection; SIS, Saline infusion sonography; HSG, Hysterosalpingography; NVOG, Nederlandse Vereniging voor Obstetrie en Gynaecologie; ESHRE, European Society for Human Reproduction and Embryology; RCOG, Royal College of Obstetricians and Gynaecologists; RCT, Randomised controlled trial; CRF, Case Record Form.
